|                             | 
 
▪ Discontinuation or temporary suspension of therapy
 
▪ Changes in white cell count, hemoglobin, platelets, creatinine, glucose, total bilirubin, alanine aminotransferase (ALT), aspartate aminotransferase (AST) over time
 
• Sub-study C: modified SOFA score, paO2/FiO2 ratio, or SpO2/FiO2 ratio
 
                                                                                                                                                                                                                                                                                                                                                                                                                                                                                                                                          |             |                             |             |                            |             |
| DESIGN / PHASE              | 
Main “antiviral therapy” study: Prospective, multicenter, randomized, open label, active controlled, platform, phase II trial. It is expected that different centers have variable access to experimental treatments and each center will randomize between open arms.
 
Substudies will be performed permitting further randomization to
 
 
• rivaroxaban vs. standard of care,
 
• angiotensin receptor blocker therapy vs. alternative anti-hypertensives
 
• asunercept (at three different doses) vs. best standard of care and
 
• Pentaglobin vs best standard of care
 
                                                                                                                                                                                                                                                                                                |             |                             |             |                            |             |

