| PATIENTS / GROUPS           | 
For the main “antiviral therapy” study currently 4 treatment arms are planned. Treatment arm 4 refers to standard of care (SOC) and will be the “control arm” of the study. A preliminary sample size calculation has been performed for the comparison of two groups based on a recent publication.
 
Therefore, we plan for n=100 patients per treatment arm in the main study. This number may increase after the interim analysis. This means that currently the main study is planned for approximately N=500 patients.
 
After inclusion of 20 and 50 patients per arm, interim analyses will be performed to draw conclusions on the sample size and to stop trial arms for safety or futility.
 
An even randomization ratio for “antiviral” arms (1:1:1:1) is theoretically intended but a dynamic assignment will occur according to available and permissible treatments (i.e. where no absolute contra-indication exists).
 |             |                             |             |                            |             |

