## 7 STUDY DESIGN

The current study design, a multi-arm adaptive platform trial, was chosen to adjust to the very dynamic circumstances of the SARS-CoV-2 pandemic. Furthermore, its design, but also the choice of endpoints, was based on the master protocol published by the World Health Organization (74). Numerous trials are currently being conducted and new information, both on trial results and on potential new experimental treatments, are being published on a daily basis. In this context, the choice of an adaptive, multi-arm platform design seems most suitable to be able to rapidly adjust to new circumstances. Some of the treatment arms may only be opened when the respective product and all necessary documentation becomes available (e.g. IVIgG). A new treatment arm will only be opened after submission of a substantial amendment. Moreover, new treatment arms may be added later and other treatment arms may be closed, if proven futile or even harmful (always with notification/submission of substantial amendments to the ethics committee or competent authorities). Since there is no established treatment for COVID-19 inclusion of a SOC arm seems justified and allows another dimension of comparison. While the SOC may differ between hospitals, it may include currently available, approved treatments for COVID-19, e.g. remdesivir and/or dexamethasone, but may also include other treatments which have been used well before remdesivir has become available. If remdesivir is not part of SOC, then patients may be randomized to receive remdesivir vs. SOC. However, since remdesivir is the only approved treatment of COVID-19, treating physicians may still decide to use remdesivir, if the clinical situation requires it. Sub-study A will only be available to patients without therapeutic anticoagulation. Sub-study B will only be opened for patients with a blood pressure >130/85 mmHg. In these patients, treatment with the lowest possible dose of candesartan is considered safe. The required dose will be titrated to normotension and may therefore be increased. However, in- and outpatients may be recruited. Two control groups will be included: Control group 1: In- and outpatients with suspicion of COVID-19, but with negative test results and control group 2: healthy volunteers with negative oral/nasopharyngeal swabs for SARS-COV-2. Sub-study C, designed to investigate immune-modulatory treatments/anti-inflammatory treatments vs. standard care ( $\pm$ placebo) will only be opened for patients with pneumonia, oxygen demand and incipient or established acute respiratory distress syndrome (in detail in in- and exclusion criteria). Patients may be included in the “main trial” or in sub-studies only. Patients may also only participate in one or more sub-studies or in the “main” antiviral part of the trial. Thus, one patient may also be eligible to more than one treatment arm.

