## 8.2 Randomization and stratification

This is a randomized trial with different active treatments. However, for this platform trial, some special circumstances need to be considered. In the “Main” antiviral study three treatment options remain active within the randomized trial. Sub-study A, B, C, will also be conducted as randomized trials against standard of care. Randomization will be carried out online by [www.meduniwien.ac.at/randomizer](http://www.meduniwien.ac.at/randomizer). No stratification will be applied, except for the asunercept part of the trial. Based on the currently known risk factors, hospitalized patients are probably older and have more comorbidities, compared to a “general population”. Moreover, the sample sizes are relatively small, which precludes further stratification due to statistical reasons.

For sub-study B randomization will occur within the treatment group. In this cohort (labelled as “sub-study B”), patients with established arterial hypertension (and treatment) may be switched and patients with blood pressure  $\geq 130/85$  mmHg will be randomized to new treatments. Importantly, those patients with blood pressure  $\geq 130/85$  mmHg but  $< 140/90$  mmHg, who are randomized to non-RAS blocking treatment will not receive any treatment. Patients will be randomized to the following two treatment options using an allocation ratio of 1:1

- RAS blocker containing treatment (candesartan)
- Non-RAS blocker containing treatment (e.g. nitrendipin/amlodipin/doxazosin)

Thus, clinicians may decide within the first 24 hours if patients who participate in the main antiviral study A will also fulfill the criteria for one of the sub-studies. It is currently not intended to simultaneously enroll a patient in sub-studies A or B. Within sub-studies randomization will be done using the same software.

For sub-study C:

Asunercept: a 3:1 randomization against standard of care will be done, whereas three different doses of asunercept will be tested. Stratification according to the WHO scale at screening will be performed (only WHO scales 4, 5, and 6 are available for inclusion (patients with oxygen demand).

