## 11 STATISTICAL METHODOLOGY AND ANALYSIS

The statistical analysis in the protocol are outlined for the main part A. More details will be provided in statistical analysis plan (SAP), which will be finalized before the first interim analysis. For sub study A, B and C separate statistical analysis plans (SAPs) will be developed. Importantly, each part of the study (e.g. Asunercept, pentaglobin, etc.) will have its own control group (randomized vs. standard of care) and will therefore be judged as an independent trial within the platform trial. Thus, the first patient in the asunercept trial is the first patient randomized to asunercept vs. standard of care and not the first patient in the platform trial. **This is necessary because background therapy is constantly changing in COVID-19 treatment such as by the introduction of remdesivir or dexamethasone.**

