### 11.2 Sample size considerations

There is currently only limited or no data available on expectable effect sizes. A preliminary sample size calculation was performed based on the primary endpoint defined as time-to-clinical improvement for the comparisons of two groups.

Based on the recent publication of Cao et al. (1) we assumed that the median time in the treatment arm 2 (Lopinavir/Ritonavir) is about 16 days. Assuming an improvement between two groups of 6 days in the median time to clinical improvement, a **log-rank test at a two-sided significance level of  $\alpha = 0.05$**  with a sample size of 100 per treatment group would yield a power larger >80%. These assumptions would translate in a hazard ratio of 1.6 when assuming exponential time-to-event curves.

The sample size calculation was performed with N-Query: When the sample size in each group is 100, with a Total number of events required, E, of 154, an exponential maximum likelihood test of equality of survival curves with a 0,05 two-sided significance level will have 83,15% power to detect the difference between a Group 1 exponential parameter,  $\lambda_1$ , of 0,069 and a Group 2 exponential parameter,  $\lambda_2$ , of 0,043, (a constant hazard ratio of 1,6).

Two interim analyses are planned. The first interim analysis is planned after 20 patients have been included in the open study arms in at least 2 groups. A second interim analysis is planned after 50 patients in a treatment arm and this can trigger a sample size re-calculation.

Possibly, treatment arms may also be closed at the interim analyses.

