## 11.6 Endpoints analysis

### 11.6.1 Primary endpoint analysis

All primary analyses will be on the modified ITT set and the analysis based on the per protocol set will be provided as supportive analysis.

The primary endpoint is time to clinical improvement which is defined as time from randomization to an (sustained) improvement of at least one category on two consecutive days compared to the status at randomization measured on a seven-category ordinal scale (proposed by WHO).

The 7-categories of the World Health Organization proposed scale, as follows:

1. Not hospitalized, no limitations on activities
2. Not hospitalized, limitation on activities;
3. Hospitalized, not requiring supplemental oxygen;
4. Hospitalized, requiring supplemental oxygen;
5. Hospitalized, on non-invasive ventilation or high flow oxygen devices;
6. Hospitalized, on invasive mechanical ventilation or ECMO;
7. Death.

During hospitalization this score will be determined daily (till day 29). If a patient is released from the hospital before day 29, the score will be determined at day 11 and 29 (and day 60 in clazakizumab arm) after randomization (depending when the patient was released or by telephone call).

The time to clinical improvement will be visualized by Kaplan-Meier Plots. The comparisons of the time-to-event curves will be performed using a log-rank at a two-sided level alpha of 5%.

(Please note in the initial phase only treatment arms (1-3, 5) might be available for the platform trial. A closed test procedure will be implemented to control the multiple level alpha. More details will be provided in the statistical analysis plan.

Additionally, a Cox-proportional hazard model will be performed. In this model we will use treatment as factor and it will be adjusted for calendar time to account for time trends (e.g. severity of cases might change over time).

Furthermore, we will include sex and age as factors in the model.

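### The primary log-rank in the antiviral study names no strata or comparator restriction, so patients who could not have been allocated to an arm can enter its comparator group

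*Protocol*

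**What the plan says.** Allocation in the main study depends on place, time and patient. The Synopsis (Design / Phase) expects that "different centers have variable access to experimental treatments and each center will randomize between open arms". Under Patients / Groups it intends an even ratio in theory, but "a dynamic assignment will occur according to available and permissible treatments". Section 7 adds "If remdesivir is not part of SOC, then patients may be randomized to receive remdesivir vs. SOC", and the update paragraph of Section 8.4 repeats that condition. Section 7.1.3 lists contraindications that remove a single arm: relevant CYP3A4/5 co-medication for lopinavir/ritonavir (arm 2), and low body weight for remdesivir (arm 3). Hydroxychloroquine (arm 1) is now inactive.

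On randomisation, Section 8.2 states "No stratification will be applied, except for the asunercept part of the trial". On analysis, Section 11.6.1 states "The comparisons of the time-to-event curves will be performed using a log-rank at a two-sided level alpha of 5" per cent, on the modified ITT set. It adds a Cox model with treatment, calendar time, sex and age. Neither centre nor the set of arms open to the patient appears in either analysis.

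Section 11 gives each part of the platform its own control group and explains: "This is necessary because background therapy is constantly changing in COVID-19 treatment".

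**The concern.** Randomisation supports a comparison of two arms only among patients who could have been allocated to either. Under this scheme some patients have zero probability of receiving a given arm, because their centre does not offer it, because it is already their SOC, or because it is contraindicated for them. They can still be allocated to another arm. A log-rank on everyone in the two arms then compares groups that differ in centre and patient mix as well as in treatment.

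The distortion can go either way. Patients kept out of arm 2 by interacting co-medication may recover more slowly, which would flatter arm 2. SOC patients at hospitals where remdesivir belongs to SOC were never candidates for arm 3. If remdesivir works, their presence would dilute arm 3 versus SOC. The net effect therefore cannot be assumed to be conservative. The Cox model's calendar-time term deals with time trends, not with these differences, and the Cox model is not the primary test.

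**Working it through.** **Step 1: the plan's own figure.** Inputs from Section 11.2: "When the sample size in each group is 100", 154 events, hazard ratio 1.6, two-sided 5%; stated result "two-sided significance level will have 83,15% power". By Schoenfeld's formula, power = Φ(√(154 × 0.5 × 0.5) × ln 1.6 − 1.96) = Φ(6.205 × 0.470 − 1.96) = Φ(0.956) = 83.05%. The stated power reproduces, so the sample-size calculation is not at fault.

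**Step 2: make-up of the comparator arm.** Assumption, not in the protocol: of all patients, a share f cannot receive arm X and is split equally over the other two of the three active arms. The rest are allocated 1:1:1. The ineligible share of one comparator arm is s = (f/2) / [(1 − f)/3 + f/2]. For f = 0.2, s = 0.1 / (0.267 + 0.1) = 27%.

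**Step 3: type I error with no drug effect.** Simulation with 100 versus 100 patients, an exponential improvement hazard of 0.043 per day (Section 11.2), daily assessment and censoring at day 29. There were 1,000 runs per cell, so the simulation error is about √(0.05 × 0.95 / 1000) = 0.7 points. Ineligible patients improve at θ times the hazard of the others; θ is also assumed.

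| f | s | θ = 0.8 | θ = 0.6 | θ = 0.5 | Co-eligible patients only, over these θ |
|---|---|---|---|---|---|
| 0.1 | 14% | 5.6% | 6.5% | 7.8% | 4.5-5.1% |
| 0.2 | 27% | 5.5% | 11.7% | 17.9% | 5.2-6.4% |
| 0.3 | 39% | 7.6% | 19.6% | 32.8% | 5.2-5.5% |
| 0.5 | 60% | 12.5% | 40.5% | 61.9% | 4.4-6.1% |

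With θ = 1 and f = 0.3 the unrestricted test gives 5.1%. For θ of 0.6 or below nearly all false positives favour arm X (at f = 0.2, θ = 0.6: 11.1 of the 11.7 points). Only θ below 1 was simulated. Comparators who improve faster would shift the error against arm X.

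**Step 4: power after restriction, comparator arm still totalling 100.** For f = 0.2 the usable comparators are 100 × (1 − 0.273) = 72.7. Events by day 28 are 100(1 − e^(−0.069 × 28)) + 72.7(1 − e^(−0.043 × 28)) = 85.5 + 50.9 = 136.4. The share in arm X is 100/172.7 = 0.579. Power = Φ(√(136.4 × 0.579 × 0.421) × 0.470 − 1.96) = Φ(0.75) = 77.4%. The same steps give:

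| f | Usable comparators | Power at hazard ratio 1.6 | Comparator arm needed for 100 usable |
|---|---|---|---|
| 0.1 | 86 | 80.7% | 117 |
| 0.2 | 73 | 77.4% | 138 |
| 0.3 | 61 | 73.2% | 164 |
| 0.5 | 40 | 61.9% | 250 |

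**The case against.** The strongest reply is that the protocol only outlines the analysis. Section 11 defers detail to a SAP due before the first interim analysis, and test strata are often settled there. That the test is unstratified and pools all patients is read from the absence of any strata or restriction in Section 11.6.1. The sentence in Section 8.2 concerns randomisation only. This stands as a caution. But the protocol itself fixes the test, the analysis set and the Cox covariates, and nothing in it points to a contrast-specific population.

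A second reply is that Section 11 already requires own controls. It does so for parts of the platform, with asunercept and pentaglobin as examples. It does not say who may be compared with whom among the arms inside the main study.

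Third, the Synopsis (Statistical methodology) reduces arm 4, which is SOC, to description only. On that reading no confirmatory SOC test exists to be inflated. However, the Synopsis also calls SOC the control arm (Patients / Groups) and has the antiviral arms tested against it (Comparative drug / control condition). The conflict is unresolved, and arm 2 versus arm 3 is exposed either way.

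A reader might infer that patients with severe hepatic impairment are barred from lopinavir/ritonavir and collect in SOC. The documents do not support this: severe liver dysfunction is a general exclusion in the Synopsis and Section 7.1.3. Allergy aside, differences between patients come down mainly to co-medication and body weight.

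A reader might also take the large error rates above as the trial's expected error. No passage gives the ineligible share or its prognosis, and the protocol commits only to two or more centres in one country.

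**Conclusion.** The point holds as a gap in the specified primary analysis. The allocation rules allow patients with no chance of receiving an arm to enter its comparator group, and Section 11.6.1 does nothing to keep them out. It applies to arm 2 versus arm 3, and to drug versus SOC if SOC is formally tested.

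The existence of the gap follows from the text; its size does not. Under the assumed inputs, two-sided type I error is indistinguishable from 5% in the mild cases (10-20% ineligible, hazard ratio 0.8) and when eligibility is not prognostic. It reaches about 20-40% with 30-50% ineligible and a hazard ratio of 0.6. These results show what the test is vulnerable to; they are not a forecast. They also assume ineligibility for one arm only, with equal allocation otherwise.

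**What to change.** 1. Have the randomiser record, for each patient, the set of arms offered at randomisation. Reconstructing this later may be unreliable.
2. In Section 11.6.1, limit each pairwise contrast to patients for whom both arms were open and permissible at randomisation.
3. Stratify the log-rank and the Cox model by the offered set, and keep the calendar-time adjustment in the Cox model. Thin strata should be manageable. With arms 2, 3 and 4, only two sets contain a given pair (with or without the third arm); counting the period when arm 1 was active, at most 2 × 2 = 4. Adding calendar-period strata on top would risk thin strata.
4. Reconcile the Synopsis statements on whether arm 4 is a tested control or descriptive only.
5. Restate the power for each contrast.

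The wording and the data export are cheap; the loss of comparators is not free. Without added enrolment, power falls from about 83% to about 77% at 20% ineligible and to about 73% at 30%. Requiring 100 co-eligible patients per arm instead would mean enrolling about 138 or 164 in the comparator arm. That is a decision on sample size rather than a wording change, so restating the reduced power is the proportionate course.

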### 11.6.2 Secondary endpoint analysis

- Clinical Status of patients according to the above-mentioned WHO scale:
  - Time to improvement of one category from admission
  - Clinical status daily
  - Mean change in the ranking on an ordinal scale from baseline
- National Early Warning Score (NEWS):
  - Time to discharge or to a NEWS of  $\leq 2$  and maintained for 24 hours, whichever occurs first
  - Change from baseline
- Oxygenation
  - Oxygenation free days until day 29
  - Incidence and duration of new oxygen use during the trial
- Mechanical Ventilation
  - Ventilator free days until day 29
  - Incidence and duration of new mechanical ventilation use during the trial
- Viral load/viral clearance
  - Baseline, and three times a week until infection has resolved
- Hospitalization
  - Duration of hospitalization
  - Duration of intensive care unit treatment
  - Intensive care unit admissions
- Mortality
  - 15-day, 29-, 60-day mortality
- Within all patients, the impact of obesity and associated diseases on mortality will be investigated (e.g. mortality, inflammatory response, duration of hospitalization, intensive care unit admission, new oxygen use, duration of oxygen)
- Treatment arm 2: drug-drug interaction analysis with lopinavir/ritonavir, in a retrospective manner
- pharmacokinetics of antiviral substances, if assays are available (e.g. lopinavir/ritonavir trough level analysis)
- Sub-study A: thromboembolic events

- Sub-study B: Renin Angiotensin System (RAS) fingerprint in patients with SARS-CoV-2 infection randomized to no RAS blocking agents, randomized to angiotensin converting enzyme (ACE) inhibitor treatment and randomized to angiotensin II blockade
  - Quality of life: EuroQoL- 5 Dimension (EQ-5D)
  - Activities of daily living/life participation, Instrumental activities of daily living scale (IADLS)
  - PROMIS social function measures
  - Dizziness
  - Gastrointestinal symptoms including nausea and vomiting (PROMIS gastrointestinal symptom scales)
  - Gastrointestinal symptom rating scale (before respiratory symptoms, many patients with COVID-19 had diarrhea, nausea, vomiting, abdominal discomfort)
  - Headache: headache impact test 6-item (HIT-6)
  - Anxiety: hospital anxiety and depression scale (HADS)
  - Fear/anxiety reported with SARS-CoV-2 infection (qualitative interview at baseline and recovery, GAD-7 scale value at all study visits [telephone or in person])
- Exploratory assessment of transaminases (including alkaline phosphatase, gamma-glutamyltransferases (GGT), aspartate aminotransferase (ASAT), alanine aminotransferase (ALAT)) and liver function parameters (including bilirubine, prothrombin time, international normalized ratio, albumin, fibrinogen) and their course during the disease and treatment
- an exploratory endpoint will encompass a comprehensive assessment of inflammatory parameters and their changes over treatment and wash out time, as well as exploratory genotype and RNA analysis with a focus on inflammation, coagulation, and the specific pathophysiology of the disease.
- Sub-study C: modified SOFA score, paO2/FiO2 ratio, or SpO2/FiO2 ratio

For **binary secondary endpoints** (such as 15 and 29 day mortality, incidence rates) absolute (n= ) and frequencies in percent (%) will be calculated per treatment group. 95%-confidence intervals will be calculated for rates, if appropriate. Such data will be visualized with bar charts. If appropriate, logistics regression model will be applied using treatment as independent factor. Furthermore, the model will be adjusted for sex and age.

For **ordinally scaled endpoints** (such as clinical status on day 3, 5, 8, 11 and 29 after admission) absolute (n= ) and frequencies in percent (%) will be calculated for all categories separately for each treatment group. Treatment groups will be compared with each other

**Continuous secondary endpoints** such as “days free of Oxygenation free days within 29” and “Ventilator free days until day 29 days” will be summarized by mean, standard deviation (SD), median, first and third quartiles, minimum and maximum for each treatment arm separately. These secondary endpoints will be analysed using an analysis of covariance (ANCOVA) using the factor treatment adjusting for the factors Sex and the covariate Age (in Years). Mean estimates will be provided, together with their corresponding two-sided 95% confidence intervals. We will conduct further explorative analyses adjusting for calendar time in the models concerned to account for time trends (e.g. severity of cases might change over time).

For **time to event endpoints** (such as time to discharge or to a NEWS of  $\leq 2$  and maintained for 24 hours, whichever occurs first) we will provide similar analyses as described for the primary endpoint.

The analyses of all secondary endpoints are considered as exploratory. Unadjusted p-values and 95%-confidence intervals might be presented for secondary endpoints, but these are for descriptive purposes only,

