| 12-lead ECG                      |          | X         |               |                    |                    |                                                                                             | X                 |                    | X, if possible                             | X, if possible                             |

|                                             |   |   |   |   |   |   |                          |                |                |
|---------------------------------------------|---|---|---|---|---|---|--------------------------|----------------|----------------|
| Laboratory Tests, incl. oropharyngeal swabs | X |   | X | X | X | X | 3x/week, until discharge | X              | X              |
| Pregnancy Test                              | X |   |   |   |   |   |                          | X, if possible | X, if possible |
| WHO-ordinal scale, NEWS                     | X | X |   |   |   |   | X                        |                |                |
| Study Drug Dispensing / Return              |   |   | X | X | X | X |                          | X              | X              |
| Adverse Events                              |   | X | X | X | X | X |                          | X              | x              |

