### 6.2 Secondary objectives

- To assess efficacy according to the National Early Warning Score (NEWS Score): time to
  - Time to discharge or to a NEWS score of  $\leq 2$  and maintained for 24 hours, whichever occurs first
  - Change from baseline until day 29, discharge or death, assessed once daily
- Oxygenation
  - Oxygenation free days until day 29
  - Incidence and duration of new oxygen use during the trial
- Mechanical Ventilation
  - Ventilator free days until day 29
  - Incidence and duration of new mechanical ventilation use during the trial
- Viral load/viral clearance using PCR-based assays.
- Hospitalization
  - Duration of hospitalization
  - Duration of intensive care unit treatment
  - Intensive care unit admissions
- Mortality
  - 15-day, 29-day, day 60 mortality, day 90 mortality
- Sub-Study A: number of thromboembolic events
- Exploratory assessment of transaminases (including alkaline phosphatase, gamma-glutamyltransferases (GGT), aspartate aminotransferase (ASAT), alanine aminotransferase (ALAT)) and liver function parameters (including bilirubin, prothrombin time, international normalized ratio, albumin, fibrinogen) and their course during the disease and treatment
- An exploratory endpoint will encompass a comprehensive assessment of inflammatory parameters and their changes during treatment and wash out time, as well as exploratory genotype and RNA analysis with a focus on inflammation, coagulation, and the specific pathophysiology of the disease (if possible for center).

- Within all patients, the impact of obesity and associated diseases on mortality will be investigated
- Safety
  - Cumulative incidence of serious adverse events
  - Discontinuation or temporary suspension of therapy
  - Changes in white cell count, hemoglobin, platelets, creatinine, glucose, total bilirubin, alanine aminotransferase (ALT), aspartate aminotransferase (AST), uric acid over time
  - Occurrence of drug induced liver injury (DILI) in various treatment arms
  - Sub-study A: bleeding events
- Treatment Arm 2: Analysis of CYP3A4 interaction of lopinavir/ritonavir with other prescribed medication in a retrospective manner

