- Sub-study B: To investigate clinical outcomes (blood pressure, dyspnea, body temperature, patient-reported fear/anxiety) and the RAS-fingerprint of patients with SARS-CoV-2 infection and arterial hypertension randomized to RAS blocking (“stay-on-any-RAS-blockade” for those patients with previously treated hypertension; candesartan for those with blood pressure  $\geq 140/90$ , measured twice after SARS-CoV-2 infection) versus non-RAS blocking treatment (nitrendipine or doxazosin).
- Sub-study C: modified SOFA score,  $paO_2/FiO_2$  ratio, or  $SpO_2/FiO_2$  ratio
- Pharmacokinetics of antiviral substances, if assays are available (e.g. trough level analysis of lopinavir/ritonavir)
- Sub-Study C for Pentaglobin: CRP, PCT, IL-6, differential blood count (baseline and day 2, 3, 7), IgM, IgA and IgG-levels (baseline, day 2, 3, 4, 5), modified SOFA score (baseline, on day 7 and day 28 of study participation)

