#### **Statistical analysis for sub-studies A-C:**

Depending on the type of endpoint, similar statistical analyses as outlined above for the main study will be performed taking only the patients included in the respective sub study. The main comparison depends on the randomization for a specific substudy. If applicable, it will be investigated whether there is an interaction with the treatments options in the main study ("antiviral" treatment arms)

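### The ANCOVA for continuous secondary endpoints adjusts for sex and age but leaves out the endpoint's own baseline value, which costs precision for NEWS change from baseline

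*Protocol*

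**What the plan says.** Section 11.6.2 sets one model for continuous secondary endpoints. They are analysed "using an analysis of covariance (ANCOVA) using the factor treatment adjusting for the factors Sex and the covariate Age (in Years". The examples are open-ended: "such as “days free of Oxygenation free days within 29” and “Ventilator free days until day 29 days". One further covariate is mentioned, and only for additional analyses: "We will conduct further explorative analyses adjusting for calendar time in the models concerned to account for time trends". Nowhere does the protocol add the endpoint's own baseline value.

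The secondary endpoints in the same section include, under NEWS, "Change from baseline". Section 6.2 spells this out as "Change from baseline until day 29, discharge or death, assessed once daily". Table 1 (Visit and Assessment Schedule) has a row "WHO-ordinal scale, NEWS" marked at screening, at randomization and during days 1 to 29, so a baseline NEWS is collected. Section 11.6.2 also lists the mean change in WHO-scale ranking from baseline.

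For the Pentaglobin part of sub-study C, section 6.2 lists "modified SOFA score (baseline, on day 7 and day 28 of study participation". For the sub-studies in general, section 11.6.2 says that, depending on the type of endpoint, "similar statistical analyses as outlined above for the main study will be performed".

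**The concern.** A patient's baseline value is usually among the best predictors of the later value and of the change. Patients with a high NEWS at entry have more room to fall, so a change score stays correlated with where it started. A model with treatment, sex and age leaves that variation in the residual. The confidence intervals that section 11.6.2 promises are then wider than the collected data allow, and any chance difference in baseline severity between arms passes into the treatment estimate.

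The design gives little other protection. Section 8.2 applies no stratification except in the asunercept part, and disease severity at entry can vary widely.

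**Working it through.** **The plan's own figure.** The protocol gives no power or precision figure for the ANCOVA endpoints. Its one power figure (section 11.2) concerns the primary endpoint: 83.15% with 154 events and a hazard ratio of 1.6 at two-sided 0.05. The Schoenfeld formula gives √154/2 × ln 1.6 − 1.96 = 2.916 − 1.960 = 0.956, that is 83.05%. The figure is reproduced, and this point does not touch it.

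**Inputs**
- Covariates: treatment, sex, age (section 11.6.2).
- Baseline NEWS: collected (Table 1).
- Pentaglobin: 20 treated plus 20 controls (section 7.1.1).
- Correlation r between baseline and follow-up, given sex and age: not in the protocol. Assumed 0.3, 0.5 and 0.7.
- Simplification: one follow-up visit, and the same variance s² at baseline and follow-up.

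**Residual variance per patient**
- Change score without baseline: s² + s² − 2rs² = 2(1 − r)s².
- Raw follow-up score without baseline: s².
- Either one with baseline as covariate: (1 − r²)s².

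**Variance ratio, with baseline against without**
- Change score: (1 − r²) / [2(1 − r)] = (1 + r)/2.
- Raw score: 1 − r².

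| r | Change score: variance ratio | 95% CI narrower by | Without baseline, n per arm matching 100 with it | Raw score: variance ratio |
|---|---|---|---|---|
| 0.3 | 0.65 | 1 − √0.65 = 19% | 100/0.65 = 154 | 0.91 |
| 0.5 | 0.75 | 1 − √0.75 = 13% | 100/0.75 = 133 | 0.75 |
| 0.7 | 0.85 | 1 − √0.85 = 8% | 100/0.85 = 118 | 0.51 |

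(The 154 patients in the first row have nothing to do with the 154 events above.)

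A simulation with 100 per arm, 2,000 runs, and sex and age in both models gave change-score ratios of 0.66, 0.73 and 0.85. An effect that has 80% power without the baseline has 93.5%, 89.9% or 86.0% power with it.

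**Chance imbalance.** With n per arm, the standard error of the baseline difference is √(2/n) SD. That is √(2/100) = 0.14 SD at 100 per arm and √(2/20) = 0.32 SD at 20 per arm. Given a baseline difference d, the unadjusted estimate moves by (1 − r)d in size for a change score and by r·d for a raw score.
- Pentaglobin modified SOFA as a raw score, d = 0.3 SD (about one standard error): 0.3r = 0.09, 0.15 or 0.21 SD at r = 0.3, 0.5 or 0.7.
- NEWS change at 100 per arm, d = 0.14 SD, r = 0.5: 0.5 × 0.14 = 0.07 SD.

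These are shifts given a particular imbalance. They average to zero over randomizations.

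**The case against.** The strongest reply is that the ANCOVA sentence follows two endpoints with no baseline value, so its covariate list is coherent as written. Placing NEWS there is then an inference: NEWS is an integer score, the only NEWS analysis that section 11.6.2 names explicitly is time-to-event, and the section has a separate group for ordinal endpoints. This stands in part. But the examples are open-ended, change in NEWS fits no other group in that section better, and the covariates are stated rather than left open. An SAP that added the baseline would be changing a stated model, not filling a gap.

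Four stronger readings are tempting, and the protocol does not support them.
- A reader might infer that modified SOFA and the two oxygenation ratios are also change-from-baseline endpoints with baselines in hand. Sections 6.2 and 11.6.2 list them as a score and ratios. A baseline is stated only for modified SOFA in the Pentaglobin part. Section 8.5.5.5 gives no time point for the ratios.
- A reader might infer that the sub-studies are bound to this model. Section 11.6.2 promises only similar analyses by endpoint type, and section 11 gives each sub-study its own SAP. The asunercept part is also stratified by WHO scale at screening (section 8.2), which limits imbalance in respiratory severity there.
- A reader might call the effect of imbalance bias. Randomization keeps the estimator unbiased, and the shifts are conditional.
- A reader might expect wrong conclusions about efficacy. Section 11.6.2 makes all secondary analyses exploratory, with p-values and intervals as description only.

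The formula is also only a guide for NEWS, which is assessed daily until day 29, discharge or death.

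**Conclusion.** The point holds for change in NEWS: the stated model omits a baseline value that the trial collects. It extends to the WHO-scale mean change if that is analysed as continuous, and to modified SOFA in the Pentaglobin part if the same model is used there.

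The loss is one of precision. Over the assumed correlations of 0.3 to 0.7, including the baseline would remove 35% down to 15% of the variance for a change score, and 9% up to 49% for a raw follow-up score. The two run in opposite directions with r, so the gain depends on which form is analysed. Under the equal-variance, single-visit simplification there is a gain throughout that range in both forms. The correlation itself is not in the protocol.

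The consequence is modest. The endpoints are exploratory, and the primary log-rank test, its power and the sample size are unaffected. The reason to act is that the improvement costs almost nothing.

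**What to change.** In section 11.6.2, state that every continuous secondary endpoint with a recorded baseline measurement is analysed with its own baseline value as a covariate, in addition to sex and age. Keep the present model for oxygenation-free and ventilator-free days. In the paragraph on sub-studies A to C, apply the same rule wherever a baseline is recorded.

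The cost is one sentence and one degree of freedom per model. NEWS needs no new data, nor does modified SOFA in the Pentaglobin part. For the oxygenation ratios, and for modified SOFA elsewhere, the rule applies only if a baseline time point is recorded.
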